# A prospective, randomized, phase II study to assess the schemas of retreatment with Lutathera® in patients with new progression of an intestinal, well-differentiated neuroendocrine tumor (ReLUTH)

**DOI:** 10.1186/s12885-022-10443-4

**Published:** 2022-12-22

**Keywords:** 177Lu-DOTA-TATE, PRRT, Neuroendocrine tumor, Overall survival, Progression-free survival, Quality of life

## Abstract

**Background:**

Although neuroendocrine tumors (NET) are classed as rare, they have a high prevalence and their incidence is increasing. Effective treatment with lutetium ^17^-[177Lu]Lu-oxodotreotide (Lutathera®) is possible in patients with well-differentiated NET, improving progression-free survival (PFS), overall survival (OS), and quality of life (QoL). However, progression does occur. Retreatment with additional Lutathera® cycles is an option to extend PFS and OS. Two retreatment cycles are usually proposed. We aim to compare four versus two Lutathera® retreatment cycles in patients with new progression of a well-differentiated intestinal NET.

**Methods:**

This will be a multicenter, randomized, controlled, open-label, phase II study in France (ReLUTH). The aim is to evaluate the efficacy of retreatment with Lutathera® in patients with progressive intestinal NET (determined by somatostatin-receptor positive imaging) after previous treatment with two cycles of Lutathera®. Before randomization, all patients will have already received two Lutathera® retreatment cycles (7.4 GBq infusion each, 8 weeks apart). A total of 146 patients will be randomized (1:1) to two additional cycles of Lutathera® (7.4 GBq infusion each, separated by 8 weeks) or to no treatment (active surveillance). Primary objective: efficacy of two additional Lutathera® retreatment cycles compared to active surveillance over 6 months. Primary endpoint: disease control rate at 6 months from randomization (defined as Complete Response, Partial Response, and Stable Disease in the Response Evaluation Criteria In Solid Tumours) with an evaluation every 2 months. A secondary objective will be the safety, as well as the PFS, OS, and QoL. It is expected that the efficacy of retreatment will increase after two additional Lutathera® cycles, with no increased safety concerns.

**Discussion:**

Our prospective, randomized controlled study may lead to new recommendations for the use of Lutathera® in patients with intestinal progressive NET, and should confirm that four cycles will be more effective than two, with limited adverse impact on safety. Four Lutathera® treatment cycles have the potential to prolong life and improve quality of life in patients.

**Trial registration:**

ClinicalTrials.gov: NCT04954820.

**Supplementary Information:**

The online version contains supplementary material available at 10.1186/s12885-022-10443-4.

## Background

Neuroendocrine tumors (NET) arise from neuroendocrine cells in the endocrine and central nervous systems. They are classified as a rare disease with a low incidence, but are becoming increasingly common. In the USA, for example, the incidence per 100,000 people has risen from 1.09 to 1973 to 6.98 in 2012 [1]. Due to the slow-growing nature of NET, they have a high prevalence, affecting 35 out of 100,000 people [1]. Two-thirds of NET occur in the gastrointestinal tract [1].

In the NETTER-1 clinical trial [2], peptide receptor radionuclide therapy (PRRT) with Lutathera® ([^177^Lu]Lu-DOTA-TATE or [177Lu]Lu-oxodotréotide every 8 weeks (four doses) plus 30 mg octreotide LAR was compared with high-dose octreotide LAR (60 mg) every 4 weeks in patients with progressive and unresectable midgut, well-differentiated (grade [G]1, G2) NET with somatostatin-receptor positive imaging (SSTRi+). At follow-up (42 months), Lutathera had improved both the median progression-free survival (PFS) (28.4 vs. 8.5 months) and median overall survival (OS) (“not reached” vs. 27.4 months). The health-related quality of life in the NETTER-1 patients showed that Lutathera had a strong, positive impact on quality of life (global health status, hazard ratio [HR] 0.406), physical functioning (HR 0.518), role functioning (HR 0.580), fatigue (HR 0.621), pain (HR 0.566), diarrhea (HR 0.473), disease-related worries (HR 0.572), and body image (HR 0.425) [3]. Therefore, Lutathera treatment was approved by the European Medicines Agency and is now reimbursed in France for this specific indication, with four intravenous injections of 7.4 GBq of Lutathera® (delivered every 2 months. More recently [4], overall survival and long-term safety results have shown that Lutathera® did not significantly improve median overall survival versus high-dose, long-acting octreotide, but the 11.7-month difference may be considered clinically relevant. Long-term follow-up did not show any new toxicity concerns.

Despite these promising results, progression will occur within a variable time in most patients, leaving limited treatment options. Retreatment with additional cycles of Lutathera® may be a possibility. A few cohort studies have been published concerning retreatment. The most recent and largest one from Van der Zwan et al. [5] showed that in patients with gastroenteropancreatic (GEP)-NET (*n* = 168) and bronchial NET (*n* = 181), the median PFS was 14.6 months after retreatment with two additional cycles of  [177Lu]Lu-DOTA-TATE and the OS was significantly longer than in the non-randomized control group. Only patients with a PFS of ≥ 18.0 months from the first administration of initial PRRT were considered eligible for retreatment PRRT. The median PFS was 14.6, 14.7, and 20 months, respectively, for the foregut, midgut, and hindgut, while the OS was 33.9, 23.1, and 56.9 months. Interestingly, safety was similar between the salvage and initial PRRT groups: no grade 3/4 renal toxicity occurred, and hematological toxicities (acute myeloid leukemia and myelodysplastic syndrome) were similar to the group of patients who received the initial treatment (four cycles). Smaller cohort studies [6–10] showed that retreatment with [177Lu]Lu-DOTA-TATE led to an improvement in survival with an acceptable safety profile (in particular, there was no increase in the incidence of renal or hematotoxicity compared to “first PRRT”), even in patients who received eight or more cycles of  [177Lu]Lu-DOTA-TATE.

Clinical practice regarding the number of new cycles is heterogeneous and most teams perform only two additional cycles (every 8 weeks), which were recently showed to be safe and effective [5]. The few studies to evaluate retreatment have been cohort studies. There is a need for a prospective trial to assess the effectiveness, safety, and quality of life after four cycles of retreatment with Lutathera® in patients with intestinal progressive SSTRi + NET, with the objective of a higher disease control rate. Accordingly, we plan to study the impact of two additional cycles compared to a controlled arm in active surveillance in the ReLUTH (retreatment with Lutathera®) trial. Different stratification factors will be used in the study, as follows: (a) the time of disease control after the “first” PRRT (< 18 months vs. ≥ 18 months) – patients with a history of a durable PFS after initial PRRT tend to have long-lasting PFS after salvage treatment (*p* = 0.04) [9]; (b) type of progression (radiologic vs. no radiologic); (c) renal function (glomerular filtration rate (GFR) < 60 mL/min vs. ≥ 60 mL/min), as it may have an impact on disease control [9] and OS [6]; (d) intercurrent line of treatment between “first” and “second” PRRT, as it is currently unclear (Yes vs. No).

The results of our prospective, randomized, controlled study may lead to new recommendations for the use of PRRT in patients with intestinal progressive SSTRi + NET. ReLUTH would provide strong statistical data to confirm that in patients retreated for intestinal progressive NET, two additional cycles of Lutathera® will be safe and effective compared to only two cycles and will have a beneficial impact on quality of life. If our hypothesis is confirmed, the results of our study would be able to prolong life and improve quality of life in patients.

## Methods

### Study design and objectives

ReLUTH will be a prospective, multicenter, randomized, controlled, open-label, phase II trial performed throughout France (Fig. 1 and Additional file 1). The primary objective will be to evaluate the efficacy of two additional cycles of Lutathera® (one injection every two months) compared to active surveillance during 6 months in patients who have already been retreated with two cycles. The primary endpoint will be the disease control rate (DCR) at 6 months from randomization (defined as Complete Response, Partial Response, and Stable Disease in the Response Evaluation Criteria In Solid Tumours (RECIST) v1.1) with an evaluation every 2 months.

**Fig. 1 Fig1:**
[figure not shown]
Study flow chart

As secondary objectives, we intend to evaluate the safety (using National Cancer Institute-Common Terminology Criteria (NCI-CTCAE) v5.0), rPFS (defined as the time from randomization until documented disease progression on radiological tumor assessment (as evaluated by an independent central review by radiologists blinded to the treatment assignments according to RECIST v1.1) or death from any cause, whichever occurs first) and PFS (defined as the time from randomization until documented disease progression on radiological tumor assessment, as evaluated in an independent central review by radiologists blinded to the treatment assignments according to RECIST v1.1), and OS (defined as the time from randomization until death from any cause). Quality of life (QoL) will also be assessed during and after treatment in both arms (assessed using the European Organization for Research and Treatment of Cancer (EORTC) QLQ-C30 and GI.NET21 questionnaires).

The expected benefit will be an increase in the efficacy of retreatment after two additional cycles of Lutathera® compared to active surveillance in patients with an intestinal NET in relapse. The risk-benefit balance of the study will be continuously evaluated by the ICM Clinical Research Pharmacovigilance Unit and discussed in the periodic safety reports.

The study was approved by a national Ethics Committee and will be performed according to Good Clinical Practice and the Declaration of Helsinki. The trial was prospectively registered on ClinicalTrials.gov: NCT04954820. The study protocol adheres to SPIRIT guidelines.

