### Statistical considerations

A median PFS of 15 months [11] after two cycles of Lutathera® for retreatment corresponds to around a 65% disease control rate 6 and 10 months from randomization and inclusion, respectively. To detect a minimal difference of 20% in disease control rate at 6 months post-randomization (65% vs. 85%) between the control and experimental groups, respectively, with a power of 80% and a 5% two-sided significance level, a total of 146 patients is required for randomization (73 patients per arm). Non-evaluable patients will be considered as failure. We estimate that around 176 patients will need to be included to ensure that 146 patients are randomized.

All analyses will be performed on an intention-to-treat (ITT) basis, defined as all randomized patients, while the safety population will comprise all treated patients who received at least one dose of treatment after inclusion. The primary endpoint will also be analyzed in the per-protocol (PP) population, defined as all eligible patients (patients with no major violations of the inclusion/non-inclusion criteria) and evaluable patients (randomized treated patients with a minimum of two evaluations).

Categorical variables will be reported with numbers and frequencies and continuous variables with medians and ranges. Qualitative variables will be compared using chi-square or Fisher’s exact tests, while quantitative variables will be compared using the Kruskal-Wallis test. The DCR will be reported using percentages and 95% confidence intervals (CI) (binomial exact method). Event-free survival (PFS, OS) will be estimated using the Kaplan-Meier method and compared using the stratified log-rank test. Statistical analyses will be performed using STATA 16.0 (StatCorp, College Station, TX, USA) and SAS 9.4 software.

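### PFS is defined without death, and the time-to-event analysis is attached to that name rather than to the adjacent rPFS definition, which includes death

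*Protocol article*

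**What the plan says.** The secondary objectives in the Protocol article (Methods, Study design and objectives, the text below Fig. 1) define three time-to-event endpoints in one sentence.

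- The first is "rPFS (defined as the time from randomization until documented disease progression on radiological tumor assessment". It is read by blinded independent central review under RECIST v1.1, and its definition closes with "or death from any cause, whichever occurs first) and PFS".
- The second is "PFS (defined as the time from randomization until documented disease progression on radiological tumor assessment, as evaluated in an independent central review", also by blinded radiologists under RECIST v1.1. Death is not mentioned.
- The third is "OS (defined as the time from randomization until death from any cause".

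Statistical considerations contains one sentence on their analysis: "Event-free survival (PFS, OS) will be estimated using the Kaplan-Meier method and compared using the stratified log-rank test". It does not mention rPFS. The article gives no other definition of PFS and no rule for a patient who dies before progression is documented. The abstract and the abbreviation list use PFS only; rPFS appears nowhere outside the secondary-objectives sentence.

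**The concern.** Progression-free survival normally ends at progression or death. Here the endpoint with that content is labelled rPFS, and the endpoint labelled PFS has progression as its only event. The analysis sentence then picks up the PFS label and describes it as event-free survival, which its definition does not deliver.

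This is more than a detail left to a fuller document. The article states the definition in full, and it conflicts both with the neighbouring definition and with the description given in the analysis section.

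Two things are at stake. A Kaplan-Meier curve built on this definition and reported as PFS would be too favourable in any arm where patients die without documented progression. Also, two near-identical definitions with one analysis sentence leave open which endpoint will be reported. In an open-label trial that choice should be fixed before the data are seen.

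**Working it through.** **1. The plan's own figure, to see whether the point touches it.** Inputs from Statistical considerations: "disease control rate at 6 months post-randomization (65% vs. 85"%), "with a power of 80% and a 5% two-sided significance level", and "a total of 146 patients is required for randomization (73 patients per arm"). The usual formula for two proportions with pooled variance and no continuity correction is

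n per arm = [1.960 × √(2 × 0.75 × 0.25) + 0.842 × √(0.65 × 0.35 + 0.85 × 0.15)]² / 0.20² = 72.4, rounded up to 73.

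The total is 146 and the power at 73 per arm is 80.3%. The stated size reproduces. No PFS definition enters the formula, so this point leaves it unchanged.

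**2. The two definitions side by side.**

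| Component | rPFS | PFS |
|---|---|---|
| Start | Randomization | Randomization |
| Progression | Radiological, RECIST v1.1 | Radiological, RECIST v1.1 |
| Reader | Blinded independent central review | Blinded independent central review |
| Death from any cause | Event | Not listed |
| Named in the analysis sentence | No | Yes |

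Death is the only substantive difference between the definitions.

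**3. Direction of the effect.** If progression is the only event, a patient who dies first leaves the risk set without an event. Each such death lowers the progression-or-death curve but not the progression-only curve. The second curve is therefore never below the first, whatever the death rate.

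**4. Size, as an illustration.** Assumptions: constant hazards; an all-cause (progression or death) median of 15 months, borrowed from the planning figure in Statistical considerations; and a share f of first events that are deaths without progression. The documents give no value for f.

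- Total hazard: λ = ln 2 / 15.
- Progression hazard: (1 − f) × λ.
- Kaplan-Meier median with deaths censored: ln 2 / [(1 − f) × λ] = 15 / (1 − f).

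| Assumed f | Calculation | Median (months) |
|---|---|---|
| 0% | 15 / 1.00 | 15.0 |
| 5% | 15 / 0.95 | 15.8 |
| 10% | 15 / 0.90 | 16.7 |
| 20% | 15 / 0.80 | 18.8 |

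**5. Effect on the comparison, also an illustration.** Suppose the hazard ratio for progression is 0.60 and f = 10% in the control arm. The hazard ratio for progression or death is 0.60 × 0.90 + HR(death) × 0.10. This gives 0.64, 0.69 or 0.74 when the hazard ratio for death without progression is 1, 1.5 or 2. The progression-only analysis shows 0.60 each time. If deaths without progression fell by the same ratio of 0.60, the two analyses would agree. The gap therefore depends on a quantity that the documents do not supply.

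**The case against.** The strongest reply is that this is a wording slip in a condensed article. The correct composite is already prespecified in the same sentence, and PFS in the analysis section may be a family label that covers rPFS. The abstract and abbreviation list, which use PFS alone, are consistent with that. The label rPFS also hints that PFS was meant to be the broader endpoint, perhaps adding the clinical or biological progression that the Patients section accepts at entry. All of this is possible, but none of it is stated, and a slip in an endpoint definition still has to be corrected.

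Three stronger readings should be resisted.

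- **That the plan has chosen to censor deaths and will leave rPFS unanalysed.** A reader might infer this. The article states no censoring rule and does not exclude rPFS from the Kaplan-Meier or log-rank analysis. Censoring follows only if the written definition is applied literally, and a fuller plan may set the rule.
- **That an excess of deaths on the additional cycles would go unseen.** It would be missing from this one curve only. Deaths count in OS and rPFS and would appear in the safety evaluation, and the pharmacovigilance unit reviews risk and benefit continuously. The primary analysis counts non-evaluable patients as failures, which probably captures deaths before the 6-month assessment as well.
- **That the result could not be compared with the cited median PFS of about 15 months.** The documents do not say how the cited studies defined PFS, so the argument has no support here.

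It is also fair to say that the larger medians above are unsupported as forecasts. The article describes these tumors as slow-growing and requires a life expectancy of at least 6 months. At f = 5% the shift is under one month.

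**Conclusion.** The definition is wrong as written. What the article calls PFS is time to radiological progression, and the only time-to-event analysis it describes is attached to that name under the description of event-free survival. Applied literally, it overstates progression-free time in that curve. The direction is certain wherever any patient dies without documented progression. The size is not known: 15.8 to 18.8 months in place of 15 for an assumed 5% to 20% of first events being deaths, under constant hazards.

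The consequence is limited. The endpoint is secondary, and the primary disease control rate and the sample size of 146 do not depend on it. This is a definition to correct before analysis, not a fault in the trial's main comparison.

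**What to change.** State that the Kaplan-Meier and stratified log-rank analysis uses time from randomization to centrally read radiological progression or death from any cause, which is the existing rPFS definition, and use one name for it throughout.

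Then either delete the second definition or rename it time to radiological progression and analyse it by cumulative incidence with death as a competing event. If PFS was intended to be broader than rPFS, for example by adding clinical or biological progression, write that definition out with death included and say which of the two endpoints the log-rank test covers.

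The cost is a corrected definition and a matching analysis sentence, made before the data are analysed. Deaths are already collected for OS, so no new data are needed, and the sample size stays at 146.

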### Patients

Recruitment began in October 2021 and will be ongoing for 3 years. The intention is to recruit 176 patients with an intestinal NET previously treated by four cycles of Lutathera® who are presenting progression (clinic, biologic, and/or radiologic) and whose retreatment with Lutathera® has been decided by a multidisciplinary tumor board (RENATEN). This number will allow 146 patients to be randomized. All patients will be followed for 60 months.

The principal inclusion criteria will be as follows: age ≥ 18 years; histologically-proven intestinal G1 or G2 NET; previous treatment with four cycles of Lutathera® (defined as “First PRRT”) and disease control after “First PRRT” ≥ 12 months; presentation of disease progression (clinic, biologic, and/or radiologic) after the first PRRT; decision to retreat with Lutathera® (defined as “Second PRRT”) validated by RENATEN and/or a multidisciplinary tumor board and in the scope of the French reimbursement process; Eastern Cooperative Oncology Group (ECOG) performance status 0–2; life expectancy ≥ 6 months, as prognosticated by the physician; SSTRi + disease within 4 months prior to randomization (may be positron emission tomography imaging [^68^Ga-based SSTR analogues] or scintigraphy imaging [^111^In-pentetreotide or ^99m^Tc-octreotide]; ≥ 90% of lesions must be SSTRi + with a significant uptake [beyond liver or surrounding tissue], measurable disease per RECIST 1.1 (Additional file 1); on CT/MRI scans, defined as ≥ 1 lesion with ≥ 1 cm in longest diameter, and ≥ 2 radiological tumor lesions in total; adequate bone marrow reserve [Hb > 8 g/dl, neutrophils ≥ 1500/mm³, and platelets ≥ 80 000/mm³]). All patients will be required to sign an informed consent before inclusion.

Principal exclusion criteria will include: no response (i.e., no complete response [CR], partial response [PR], or stable disease [SD]) to “first PRRT”; radiological progression after two cycles of “Second PRRT” according to RECIST version 1.1; G4 hematotoxicity and/or nephrotoxicity during the initial PRRT, or unresolved adverse events categorized as G2 or higher (as per the CTCAE v5.0 from previous PRRT cycles or any other therapy for NET, excluding alopecia and peripheral neuropathy); pancreatic NET; neuroendocrine carcinoma; patients with prior external beam radiation therapy to > 25% of the bone marrow; severe renal impairment (GFR according to the Modification of Diet in Renal Disease < 40 mL/min or nephrotic syndrome) or hepatic insufficiency (alanine aminotransferase/aspartate aminotransferase > 2.5 x the upper limit of normal [ULN], or > 5 x ULN if liver function abnormalities are due to the underlying malignancy, and/or total serum bilirubin > 2.5 x ULN); any other uncontrolled concomitant disease or brain metastases (unless they have been treated and stabilized for at least 24 weeks prior to enrolment in the study; patients with a history of brain metastases must have had a head CT scan with contrast or MRI to document stable disease prior to enrolment in the study); history of another solid tumor in the 5 years before inclusion, apart from treated and controlled cancer in the cervix and skin cancer (basal or squamous cell).

